### Outcomes

Tables 1 and 2 show the maternal and infant primary and secondary outcomes at the different time points. Table 3 shows the additional information, such as the demographics and confounders that will be collected in the current study.

**Table 1 Tab1:** Maternal outcome measures

Construct	Timing (W = week/Y = Year)				Measure	Additional information
	W2	W5	W12	Y1		
Primary outcome						
1. Mental health						
1.1 Depressive symptoms	x	x	x	x	Edinburgh Postnatal Depression Scale (EPDS)	10-item validated questionnaire to screen for depressive symptoms in a post-partum setting [53].
Secondary outcomes						
1. Mental health						
1.2 Anxiety	x	x	x	x	State-Trait Anxiety Inventory (STAI)	The STAI is a 40-item validated questionnaire to screen for anxiety [54].
1.3 Stress	x	x	x	x	Alledaagse Problemen Lijst (APL)	The APL is a 49-item validated questionnaire to assess the occurrence and intensity of daily hassles [55].
1.4 Traumatic Stress following child birth	x	x	x	x	Traumatic Event Scale-B (TES-B)	The TES-B is a 35-item validated questionnaire to examine traumatic stress after giving birth to a child [56].
1.5 Sleep quality	x	x	x	x	Adjusted version of the Karolinska Sleep Diary (KSD) & Pittsburgh Sleep Quality Index (PSQI)	Every morning, for three consecutive days, the mother will fill in the KSD starting at week two, five and twelve [57]. In addition, questions related to daytime sleep and reasons for wakening will be included. At twelve weeks and one year, the mother will fill in de PSQI [58]. The PSQI is a 19-item validated questionnaire to examine sleep quality and disturbances in reference to their sleep during the past month.
2. Physical health						
2.1 Physical recovery related to the delivery	x	x	x	x	Maternity carer logbook & Multidimensional Fatigue Inventory (MFI) & Bodily Pain subscale of the Short-Form Health Survey (SF-36)	The maternal physical recovery logbook of the maternity carer from the first week after birth will be copied at the second home visit. The MFI is a 20-item validated questionnaire to examine fatigue [59]. The two-item subscale of the SF-36 will be used to examine bodily pain [60].
2.2 Health		x	x	x	Health interview & questionnaire	A maternal health interview, based on the infant health interview [61], will be performed during the second home visit. During the follow-up assessment the mother will fill out health questionnaires, based on the infant health interview [61].

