Medical checklist	x					During the telephone call in pregnancy the medical checklist will be filled out to examine severe physical and mental health problems. In addition, eligibility questions will be answered: age, language proficiency, singleton versus twin pregnancy.
Self-developed delivery questionnaire		x				Infant weight, Apgar, birth and delivery complications, born ≥37 weeks of pregnancy
Demographics						
Demographics questionnaire	x					Maternal age, educational level, SES, drugs use, alcohol use, smoking, number of siblings, age of siblings.
Self-developed delivery questionnaire		x				Infant sex.
Physical contact						
Daily logbook/weekly logbook/questionnaire on physical contact		x(w1–12)			x	Mothers will register 1) holding, 2) SSC, and 3) no contact, as three distinct behavioural categories, for every 15 min with simple lines for the first 5 weeks after birth. In the daily logbook, mothers are able to discriminate between holding and SSC by the mother or other caregivers. Between week 5 and week 12, all mothers will note the estimated time spent in daily holding and SSC on a weekly basis. During the follow-up assessment at 1 year after birth, mothers will indicate how many weeks after week 12 they provided SSC to their infant.
SSC protocol adherence						
Maternal prenatal depressive symptoms, anxiety, and stress	x					The EPDS to screen for depressive symptoms [53]. The Pregnancy-Related Anxieties Questionnaire-Revised (PRAQ-R) is a 34-items validated questionnaire to screen for pregnancy related anxieties [71]. The STAI to screen for anxiety [54]. The Pregnancy Experience Scale (PES) is a 43-items validated questionnaire to assess perceived maternal appraisal of pregnancy-related daily hassles [72]. A 20-item self-developed questionnaire to examine worries related to the preparation for the baby’s arrival. The APL to screen for the occurrence and intensity of daily hassles [55].
Mother-infant bond	x					The Maternal Antenatal Attachment Scale (MAAS) is a 19-item validated questionnaire to assess maternal attitudes, thoughts, and feelings towards the unborn child [73].
Self-developed delivery questionnaire		x				Number of days the father stayed at home after birth.

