Weekly logbook sleep location & night awakenings		x(w1–12)				The mother will register the primary sleep location of the infant during 00.00–05.00 h for the previous week [47, 74]. Also, the average number of night awakenings of the infant between 00.00–05.00 h will be noted in the weekly logbook.
Parental ethnographies questionnaire	x		x			10-item questionnaire to assess cultural conceptions on parenting [75].
Social support questionnaire	x		x			Adjusted version of the Social Support Effectiveness Questionnaire (SSE-Q) to examine instrumental, informative and emotional partner support, and negative affect [76].
Social touch			x			The Social Touch Questionnaire (STQ) is a 20-item questionnaire to assess attitudes towards social touch [77].
Adult attachment			x			The Experiences in Close Relationships Scale (ECR) is a validated 36-item questionnaire to asses adult attachment to her current and previous partners [78].

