### Randomization

Primiparous mothers are expected to have more opportunities to provide SSC to their infants compared to multiparous mothers. A stratified random block randomization method will ensure a balance between the SSC and the control condition for the primiparae versus multiparae mothers. Also, this randomization method produces comparable groups by avoiding confounding from known and unknown factors [49]. The block sizes will be randomly chosen from the set of 4 and 6. Randomization will be with a 1:1 allocation. An independent researcher, who is not involved in the study, will prepare this schedule by a computerized randomisation program and will conceal the allocation sequence in stapled envelopes. The allocation sequence will be concealed from the researcher enrolling and assessing participants. The mothers will be included in the study after signing the informed consent, regarding the use of participant data and biological samples (see Additional file 3 for the Dutch versions of the informed consent form and information statement for participants), and filling out the medical checklist during the pregnancy home visit. Hereafter, the principal investigator will open the envelope and the mothers in the SSC group will be informed about their group allocation. Participants and the principle investigator will not be blinded for the group allocation.

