### Pregnancy home visit

One day before the pregnancy home visit, an e-mail will confirm the home visit. During this visit, the researcher reconfirms eligibility. Based on the cover story, the experimenter will provide additional information about the study. If mothers are still interested, informed consent is obtained by the principle investigator and mothers will fill out the medical checklist. Next, the SSC group will be informed about the group allocation. Expectant mothers in the SSC group will receive detailed instructions on SSC. All expectant mothers will receive the information statement with a summary of the instructions about the prenatal and postnatal part of the study. Also, the experimenter will explain how the study logbooks and questionnaires need to be filled out, and how the samples need to be collected. Additionally, the mother will be asked about her preference related to the communication during the intervention period (e-mail versus text-message). Lastly, the mother will fill out the prenatal questionnaires.

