### Data-analysis

Data will be handled according to standard procedures. Demographic characteristics and study outcomes will be described for each treatment group using means and standard deviations for continuous outcomes. Proportions for categorical data will be provided. The pattern of missingness will be checked before the analyses. All measures will be controlled for outliers and checked for normality. Skewed continuous outcomes will be transformed. The level of significance (*p* -value) is set at *p* < .05 in all analyses.

We will conduct intention-to-treat analyses, in which participants are compared according to the group they were randomly assigned to regardless of participants’ compliance, including SSC protocol adherence, or withdrawal from the study, and analyses on imputed datasets based on the multiple imputation method [52]. Primary and secondary outcomes, that will be examined once, will be compared within multivariate analyses of covariance. Multilevel mixed models will be used for repeated measures. Microbiota composition will be examined with the Pearson’s moving window correlation. Microbiota diversity will be calculated with the Simpson’s reciprocal index of diversity (1/D). The Benjamini and Hochberg method will analyse differences between the SSC group and the control group. The analyses will be adjusted for potential confounding factors identified a priori (see Table 3). Structural equation models will be used to examine the mediation effect of the potential underlying mechanisms, maternal oxytocin concentrations and infant intestinal microbiota, on maternal and infant outcomes, respectively.

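### The adjustment set is fixed only by pointing to Table 3, which mixes prenatal variables with variables recorded after allocation, so adjustment may move the group effect away from the ITT effect

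*Protocol article*

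**What the plan says.** The Data-analysis section of the protocol article commits to intention-to-treat: "participants are compared according to the group they were randomly assigned to regardless of participants’ compliance, including SSC protocol adherence". The same paragraph then states: "The analyses will be adjusted for potential confounding factors identified a priori (see Table 3"). The sentence makes no exception for any outcome and no distinction by time of measurement.

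The Outcomes section describes the table more broadly: "Table 3 shows the additional information, such as the demographics and confounders that will be collected in the current study". Confounders are thus one part of Table 3. In the text available, no heading marks which rows they are.

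Allocation is disclosed at the pregnancy home visit. Under Randomization, after consent and the medical checklist: "Hereafter, the principal investigator will open the envelope and the mothers in the SSC group will be informed about their group allocation". The section on that visit puts SSC instruction next and ends: "Lastly, the mother will fill out the prenatal questionnaires".

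**The concern.** A variable recorded after allocation cannot confound a randomised comparison, because it cannot have influenced who was allocated to what. It can, however, be a consequence of the allocation. If SSC changes such a variable and the variable is related to the outcome, conditioning on it removes the part of the effect that runs through it. If the variable also shares unmeasured causes with the outcome, conditioning adds a further distortion that can go either way. The group coefficient is then not the ITT effect promised in the same paragraph. Choosing the variables a priori guards against selective choice but not against this. The sentence covers the primary EPDS model as well as the secondary ones.

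**Working it through.** **Step 1. Which rows could be meant.** Leave out the eligibility, demographic and physical-contact rows of Table 3. Eight rows remain:

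| Row | Timing in Table 3 | Before allocation? |
|---|---|---|
| Prenatal depressive symptoms, anxiety, stress | Pregnancy | Same visit, but after disclosure as now ordered |
| Antenatal mother-infant bond | Pregnancy | As above |
| Parental ethnographies | Pregnancy and week 5 | Depends on the value used |
| Social support | Pregnancy and week 5 | Depends on the value used |
| Father's days at home | Week 2 | No |
| Sleep location, night awakenings | Weeks 1–12 | No |
| Social touch | Week 5 | No |
| Adult attachment | Week 5 | No |

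Four of eight are recorded only after birth, and two more are ambiguous. The sleep row is logged through and beyond the five-week intervention ("The mother will register the primary sleep location of the infant during" the night hours, plus the number of awakenings). The touch row ("The Social Touch Questionnaire (STQ) is a 20-item questionnaire to assess attitudes towards social touch") is filled in at the end of five weeks of requested daily contact.

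**Step 2. Which of these SSC could move.** The Objectives hypothesise better infant sleep under SSC, and Table 2 makes infant sleep quality a secondary outcome. On the protocol's own account, night awakenings are therefore close to a treatment effect. An SSC effect on touch attitudes is plausible but not stated. None is stated for attachment or for father's days at home.

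**Step 3. Size of the bias under assumptions.** The planned effect is f = .24, which for two equal groups is d = 2 × .24 = 0.48 SD; the true effect on EPDS is taken as −0.48. Let SSC shift the covariate by *a* SD and the covariate change the outcome by *b* SD per SD. With no shared cause, the adjusted coefficient is −0.48 − *ab*. The values of *a* and *b* are assumed. A simulation of this model agreed with the formula.

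| *a* | *b* = −0.1 | *b* = −0.3 |
|---|---|---|
| 0 | −0.48 | −0.48 |
| 0.2 | −0.46 | −0.42 |
| 0.5 | −0.43 | −0.33 |
| 1.0 | −0.38 | −0.18 |

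Now add an unmeasured cause that loads 0.4 on both covariate and outcome. This adds −0.4 × 0.4 × *a* = −0.16*a*. With *a* = 1.0 and *b* = −0.1 the result is −0.48 + 0.10 − 0.16 = −0.54, so the effect is exaggerated rather than diluted. With *a* = 0 there is still no bias.

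**Step 4. Power, as illustration only.** The article gives N = 84 for 80% power but neither the number of occasions nor their correlation. With *m* occasions and correlation ρ, λ = f²·N·m / (1 + (m − 1)ρ), on 1 and N − 2 degrees of freedom. Five occasions (pregnancy plus four postnatal) and ρ = .5 give λ = .0576 × 84 × 5/3 = 8.06 and power 80.1%, which matches the stated figure. Three occasions with ρ = .4 also return 84. The four postnatal occasions of Table 1 with ρ = .5 give 78.5%.

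Under the five-occasion assumption, suppose a share of the effect runs through an adjusted covariate and residual variance is unchanged:

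- 20%: f = .192, power 61.2%
- 30%: f = .168, power 50.2%
- 50%: f = .12, power 28.9%

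**The case against.** The strongest reply is that a condensed article need not list covariates model by model, and that the word potential marks only a candidate set. That is fair as to detail. But the article does more than stay silent: it names the source of the set, and that source contains post-allocation variables with no limit on timing.

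A second reply is that bias needs SSC to move the covariate. This stands. Adult attachment may be largely trait-like, the documents hypothesise an SSC effect only for infant sleep, and parental ethnographies and social support could be used at their pregnancy values.

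A reader might infer that SSC time itself is a covariate, since Table 3 includes the contact logbook ("Mothers will register 1) holding, 2) SSC, and 3) no contact, as three distinct behavioural categories"), and that the group effect would then shrink towards zero. The documents do not support this. The logbook stands under its own heading, confounders are only part of the table, and the analysis paragraph compares groups regardless of adherence. A confounder heading may also have been lost when the table was converted to text. For the same reason, age of siblings and drug use, both in the demographics row, are not shown to be model covariates.

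**Conclusion.** The concern holds in a limited form. As written, the rule allows the ITT models to be adjusted for at least four rows recorded only after birth, and leaves the timing of two more open. For night awakenings the conflict is direct, because they overlap a secondary outcome that SSC is hypothesised to improve. For the others, bias is possible but not shown. It would be wrong to say that the SSC effect is biased: it may be, by an amount the documents do not determine and in either direction. The figures above rest on assumed shifts, coefficients, occasions, correlation and mediated shares, and only show scale.

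A related weakness affects the obvious substitute. In the stated order of the home visit, the prenatal questionnaires, prenatal EPDS among them, follow disclosure of allocation to the SSC group in an unblinded trial. They are not yet clean baselines.

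**What to change.** Replace the adjustment sentence with one to this effect: ITT models for primary and secondary outcomes are adjusted only for parity (the randomisation stratum) and for a named list of Table 3 variables measured in pregnancy, including prenatal EPDS for the primary outcome and, if social support or parental ethnographies are used, their pregnancy values. Variables first recorded after birth enter no ITT model and are kept for descriptive, exploratory or mediation analyses, labelled as such.

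In the description of the pregnancy home visit, place the prenatal questionnaires before the envelope is opened. For visits already held in the present order, report that these values were taken after disclosure, and show the primary result adjusted for parity alone alongside.

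The cost is a short rewording of the adjustment rule and a change of order within one visit. No new data or extra participants are needed.

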### Dissemination

Data will be analysed when all the data is collected. The principal investigators will make every attempt to reduce the interval between the completion of data collection and the release of study results to a minimum. The principle investigators will justify names for authorship regarding topics suggested for presentation or publication. Data will only be reported study-wide. The study results will be released in a study-wide manner to participants after publication of the results. Also, the study results will be released to the general public by several channels, including international high impact journals and, at a national level, by oral presentations in health care organizations to inform nurses, midwifes, pediatricians and mental healthcare practitioners about this intervention method.

## Discussion

Maternal depressive symptoms in the postpartum period are highly prevalent and affect the mother and child in the short-and long-term. Most of these mothers remain untreated for a long period of time or are not treated at all. There is great need for simple and cost-effective prevention and (complementary) intervention methods that are easily accessible to mothers and that can be applied immediately after birth. SSC is such a low-cost intervention that it would be accessible, simple, and feasible for most mothers in the first postpartum weeks.

In preterm infants, SSC has been shown to be beneficial for the mother and the infant in reducing maternal postpartum depressive symptoms. Additionally, the preterm infant grows quicker and is healthier, cries less and sleeps better, while mothers are less anxious and stressed, invest more in breastfeeding, and feel more bonded to their infant. SSC may be a promising method for mothers and their full-term infants as well. To date, most studies have focused on preterm infants or on SSC in full-term infants during the first postnatal hours. If SSC is shown to be effective in reducing depressive symptoms in low-risk mothers of infants born full-term, then an SSC intervention could potentially be investigated in high-risk samples of prenatally and postnatally depressed mothers who should be carefully screened (e.g. for touch aversion) and closely monitored and supported during the intervention period. Also, thought could be given to developing programs using SSC in a preventive manner. SSC may also constitute a cost-effective prevention program for mothers and their children enhancing and strengthening developmental processes. Finally, by exploring two possible underlying mechanisms of SSC, this study will additionally provide important and innovative scientific knowledge that will deepen our understanding of the biology underlying mother-infant skin-to-skin contact and dyadic interactions.

## Abbreviations

APL: Alledaagse Problemen Vragenlijst
ASQ-3: Ages & stages questionnaire, third edition
AUC: Area under the curve
BISQ: Brief infant sleep questionnaire
BITSEA: Brief infant toddler social emotional assessment
ECR: Experiences in close relationships
EPDS: Edinburgh postnatal depression scale
HPA: Hypothalamic-pituitary-adrenal
IBQ-R: Infant behavior questionnaire revised
KSD: Karolinska sleep diary
MAAS: Maternal antenatal attachment scale
MFI: Multidimensional fatigue inventory
MPAS: Maternal postnatal attachment scale
NTR: Dutch trial registration
PES: Pregnancy experience scale
PRAQ-R: Pregnancy-related anxieties questionnaire revised
PSQI: Pittsburgh sleep quality index
RCT: Randomized controlled trial
SF-36: Short-Form Health Survey
SSC: Skin-to-skin contact
SSE-Q: Social support effectiveness questionnaire
STAI: State-trait anxiety inventory
STQ: Social touch questionnaire
TES-B: Traumatic event scale – B
